#### Physical activity

The IPAQ (International Physical Activity Questionnaire) validated for the Brazilian population will be used to assess physical activity levels [51]. After being measured, the outpatients will be instructed not to change their physical activity patterns.

#### Prescribed medications

As described in the eligibility session, only patients under anti-inflammatory therapy will be excluded. There are no restrictions for any other medications; however, any alteration on prescribed medications will need to be immediately communicated.

#### PBMC isolation

After blood collection into heparinized tubes, the samples will be prepared with the use of histopaque-1077 (Sigma, St. Louis, MO, USA). In brief, 15 mL of the blood will be carefully layered onto 15 mL of histopaque. Bands containing the mononuclear cells, leukocytes, and red cells will be collected separately. The PBMCs will be washed with saline, centrifuged, and the supernatant removed [52]. This step will be repeated twice, and three parts of the cell suspension will be destined for immunoblotting/immunoprecipitation, RT-qPCR, and lipid profile analysis. Neutrophils and red blood cells will be lysed using a standard lysis buffer and re-suspended in Trizol® reagent (Life Technologies), storing at −80 °C for RT-qPCR analysis.

#### Immunoblotting and immunoprecipitation analysis

After isolation, PBMCs and neutrophils will be immediately homogenized in solubilization buffer at 4 °C [1% Triton X-100, 100 mmol/L Tris–HCl (pH 7.4), 100 mmol/L sodium pyrophosphate, 100 mmol/L sodium fluoride, 10 mmol/L EDTA, 10 mmol/L sodium orthovanadate, 2.0 mmol/L PMSF, and 0.1 mg aprotinin/mL]. For these cells or plasma proteins, the quantification of total protein will be carried out according to the bicinchoninic acid method [53]. Samples containing 50 μg of protein extracts will be separated by SDS–PAGE, transferred to nitrocellulose membranes, and blotted with antibodies against inflammatory markers: TNFα, MCP1, IL1β, IL6, IL10, JNK, and TAK1; ER-stress markers: ATF1, ATF6, IRE1, XBP1, CHOP, eIF2α, and eIF4; and ω3 pathway markers: GPR120, βarr2, and TAB1/2. In some experiments, the association between GPR120 and βarr2 or βarr2 and TAB1/2 will be evaluated by performing immunoprecipitation. Samples of total protein extracts containing 200 μg of protein will be used for immunoprecipitation with antibodies against GPR120, βarr2, or TAB1/2 and protein G-sepharose at 4 °C overnight, followed by SDS/PAGE and will be transferred to nitrocellulose membranes and blotting with respective antibodies. The bands will be labeled by chemiluminescence and its visualizations performed by GBOX-Chemi-XX6 from Syngene® (Cambridge, Eng).

#### Gene expression

Leukocytes and PBMCs re-suspended in Trizol® reagent (Life Technologies) will be submitted to RNA extraction according to the manufacturer’s instructions. Reverse transcription reaction will be performed using a commercially available set of High Capacity cDNA Archive Kit (Applied Biosystems, USA). The cDNA will be prepared from 1 μg of mRNA, with random hexamer primers, for 10 min at 25°C, 2 h at 37 °C, and 4 °C thereafter on a PCR thermocycler Gene (Applied Biosystems, USA). The resulting cDNA will be diluted to a final concentration of 5 ng/μL to constitute a matrix in further experiments. For real-time quantitative PCR amplification, the TaqMan system (Thermo Scientific®) using specific probes and primers (*Tnfα*, *Il1β, Il6, Il10, Ire1, Perk,* and *Atf6*) gene evaluation will be used, and *Gapdh* will be used as a constitutively expressed gene in these cells. The 7500 real-time qPCR equipment (Applied Biosystems®) will perform fluorescence readings. Expression levels of the target gene transcribed in each sample will be calculated by the comparative Ct method (formula 2^ΔCt^) after normalization with the endogenous gene (*Gapdh*) from Applied Biosystems®.

#### *Gpr120* gene polymorphism—R270H variant

The GPR120 gene variant R270H (rs116454156) polymorphism will be genotyped using the Taqman allelic discrimination technique in the 7500 real-time qPCR equipment (Applied Biosystems®), following the method proposed by Ichimura et al. (2012) [36].

#### Omega-3 fatty acid determination from capsules, blood, and cells

Fifty μL of oil obtained directly from ω3 capsules will be submitted to saponification and esterification following the method of Hartman and Lago [54]. To determine the free fatty acid profile from the blood, 150 μL of the plasma will be directly methylated according to the previously described procedure (Shirai et al., 2005) [55]. Fatty acid methyl esters will be analyzed using a gas chromatograph coupled to the mass spectrometer (model GCMS-QP2010 Ultra; Shimadzu) and a fused-silica capillary Stabilwax column (Restek Corporation, U.S.) with dimensions of 30 m × 0.25 mm internal diameter coated with a 0.25-μm-thick layer of polyethylene glycol. The experimental conditions will be followed by the method described by Cintra et al., 2012 [4].

#### Data treatment and statistical aspects

A steering committee will be organized for trial supervision. The process of data collection and management will be monitored by them. The committee may recommend and request the principal investigator to make some changes to the plan. To increase the security and data quality, the records will be inputted at the bank by one person and checked by another one. Data analysis will be performed according to the intention-to-treat principles [56]. The software Statistical Package for Social Sciences (SPSS), v. 22.0, will be used for data entry and analysis. Statistical analysis will be performed through descriptive analysis, with numerical variables expressed as the mean and standard deviation (SD) or median and interquartile range. All data will be subjected to the Shapiro-Wilk normality test. First, a two-way analysis of variance will be performed to check intra- and intergroup differences. Time will be added as a repeated factor, treatment as an independent factor, and the other variables (e.g., anthropometric data, food intake, blood analysis) as covariates.

The paired Student’s *t* test or Wilcoxon’s test will be used to compare the time effects. The Student’s *t* test and Mann-Whitney *U* test will be used to investigate group differences (placebo and treatment). All tests will be considered significative *P*<0.05. After trial completion, the principal investigator (PI) will be responsible for data archiving and preservation. Only investigators can access data. The PI will be responsible to terminate the trial at any moment.

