### Sample size calculation

The sample size calculation was carried out using the G * Power 3.1.9.2 software, and the following values and information were considered: [1] two groups (control and treatment) and [2] effect size *d* = 1.15 considering the variation of TNFα/βactin protein observed in the study by Huang et al. (2016) [39]. In this study, the control group showed 0.45±0.04 (average of arbitrary units ± standard deviation) for TNFα while the telmisartan treated group showed 0.36±0.04 [39]. As in the reference study [39], three types of drugs were used (telmisartan, cyclosporine, and 4-aminopyridine), and the least effective was chosen, understanding that eating will have a possible minor effect concerning hypertensive drugs. This procedure may reduce type II error, [3] type I error *α* = 0.05, and [4] sampling power (1 - *β*) = 85% [5]. The sample size needed was 16 individuals in each group. However, considering a 40% dropout rate, it will be selected 22 per group.

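### The plan claims intention-to-treat, but its named tests use only participants with a day-28 value (about 13 of 22 per arm at 40% dropout), and none is stated to adjust for the baseline marker

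*Protocol article*

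**What the plan says.** All of the inferential plan is in the section on data treatment and statistical aspects. The principle is "Data analysis will be performed according to the intention-to-treat principles". The methods follow:

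- "First, a two-way analysis of variance will be performed to check intra- and intergroup differences". In this model, "Time will be added as a repeated factor, treatment as an independent factor". Anthropometric, dietary and blood variables are given as examples of covariates.
- For change within a group, the paired t "test or Wilcoxon’s test will be used to compare the time effects".
- Between groups, the t test and the Mann-Whitney "test will be used to investigate group differences (placebo and treatment").
- SPSS 22 is the software.

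The sample size section expects heavy loss: "However, considering a 40% dropout rate, it will be selected 22 per group". Under study design, the chronic primary outcome is the reduction in TNFα and IL6 protein in PBMCs after 28 days. Under procedures, the only chronic-phase reassessment is the last meeting.

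**The concern.** A participant who leaves before the last meeting has no day-28 marker value, and none of the named tests can use such a participant as it stands. A classical repeated-measures ANOVA deletes incomplete cases, a paired test needs both values, and a day-28 group test needs the day-28 value. Any covariate with missing values removes more people from the ANOVA.

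Two things are at stake. First, a reader will take the intention-to-treat label to mean all 44 randomised participants, when roughly 18 may be absent from the primary comparison. Second, if those who stay differ between arms in baseline inflammation, neither an unadjusted day-28 comparison nor an unadjusted comparison of changes corrects for it. The protocol gives some reason to think about unequal loss: it expects eructation with an unpleasant odour and associates eructation with omega-3, while the placebo is mineral oil. The acute 3-hour comparison is largely unaffected.

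**Working it through.** **1. The plan's own figures.** Inputs from the sample size section: d = 1.15, α = 0.05 (taken as two-sided), power 85%. A two-sample t test needs 14.6, so 15 per group. Allowing for Mann-Whitney efficiency gives 15.3 to 16.9. The stated 16 is reproduced within that range. The stated 22 is 16 × 1.4 = 22.4, rounded down.

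**2. Who is analysed.** 22 × (1 − 0.40) = 13.2 per arm. In total 44 × 0.60 = 26.4 are analysed and 44 − 26.4 = 17.6 are not. With 13 per arm, t-test power at d = 1.15 is 80%, against the planned 85%.

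**3. Size of a possible bias.** The documents give no dropout mechanism, so this one is assumed:

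- The marker is standardised, with correlation ρ = 0.5 to 0.7 between baseline and day 28, and there is no true effect.
- In the placebo arm, dropout is 40% at random.
- In the ω3 arm, logit P(dropout) = −0.49 + 1 × baseline, which averages 40%.

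The mean baseline of ω3 completers is m = ∫ z[1 − p(z)]φ(z)dz / 0.60 = −0.33 SD. The placebo mean is 0. Therefore:

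- day-28 difference: ρ × m, which is 0.5 × (−0.33) = −0.17 and 0.7 × (−0.33) = −0.23;
- difference in change (the time × treatment term with two times): (ρ − 1) × m, which is +0.17 and +0.10;
- baseline-adjusted difference: 0.

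Lower values are better, so a negative bias favours ω3 and a positive bias counts against it.

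**4. Simulation of the same setting**, 22 per arm, all three analyses run on the same completers (10,000 runs per correlation):

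| Analysis | Bias (SD), ρ = 0.5 / 0.6 / 0.7 | Type I error | Empirical SE |
|---|---|---|---|
| Day-28 t test | −0.17 / −0.20 / −0.23 | 7.0% / 7.3% / 8.7% | 0.39 / 0.39 / 0.39 |
| Change (time × treatment) | +0.16 / +0.14 / +0.10 | 7.0% / 6.5% / 6.1% | 0.39 / 0.35 / 0.31 |
| Baseline-adjusted (ANCOVA) | 0.00 / 0.00 / 0.00 | 4.9% / 4.8% / 5.0% | 0.36 / 0.33 / 0.29 |

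Allowing for simulation error, the working ranges are −0.16 to −0.24 SD with type I error of about 7% to 10% for the t test, and +0.10 to +0.17 SD with about 6% to 8% for the interaction.

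**5. Other mechanisms.** With 40% random dropout in both arms, or dropout depending on baseline equally in both arms, all three analyses have bias of about 0 and type I error of about 5%.

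**6. Precision.** The t-test SE is about √(2/13.2) = 0.39. Baseline adjustment multiplies it by about √(1 − ρ²), giving 0.34 at ρ = 0.5 and 0.28 at ρ = 0.7. The simulated 0.36 and 0.29 are slightly larger, as expected in samples this small.

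**The case against.** The strongest reply is that the article never says completers only. Analysing people in their randomised arm, which is one accepted meaning of intention-to-treat, is not contradicted. A full protocol or analysis plan could impute before running the same tests, and a repeated factor could be fitted as a mixed model. Silence about missing data in a condensed article is not a fault.

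Most of this stands. A reader might infer that the plan breaks randomisation or excludes dropouts by rule; it does neither. What remains is that the article fixes both a principle and a set of tests. Run as named, at the article's own dropout rate, those tests leave out about two in five of those randomised.

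A second reply also has force: the simulated bias disappears when the same completers are analysed with baseline adjustment. The figures therefore show the cost of not adjusting for baseline, not the cost of analysing completers as such. The point is framed accordingly.

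Third, the mechanism is assumed. The documents do not link eructation to withdrawal or withdrawal to baseline inflammation, and weekly calls are planned partly for retention.

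**Conclusion.** The point holds in a limited form. The named tests do not deliver an analysis of all randomised participants: about 26 of 44 contribute to the day-28 comparison at 40% dropout. No group comparison is stated to adjust for the baseline marker. The covariate examples do not name it, and in a two-time repeated-measures ANOVA it is one of the two outcomes.

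The bias is conditional. It needs dropout that depends on baseline differently by arm. Under the assumed mechanism it is modest, and it has opposite signs in two analyses that the plan names. A reader might infer that the trial is tilted towards ω3. The documents do not support that: the first-named analysis, the time × treatment ANOVA, would be tilted against it, and under equal or random dropout there is no tilt. The gain in precision from baseline adjustment does not depend on the dropout mechanism; it rests only on the assumed correlation.

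**What to change.** - **Primary comparison.** State that the day-28 group comparison is adjusted for the baseline marker value. Use ANCOVA, or a linear mixed model in SPSS with a common baseline mean that includes every randomised participant with any sample. With a single chronic follow-up visit the two should agree closely. A log scale is optional.
- **Follow-up.** Seek the day-28 sample from participants who stop capsules but have not withdrawn consent. Only this step reduces the number of missing outcomes.
- **Sensitivity.** Add one analysis for data not missing at random, such as delta-adjusted multiple imputation.
- **Wording.** Describe the analysis as all participants with available data, in their randomised arm, not as full intention-to-treat.

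The cost is a change of analysis wording and some extra contact and day-28 draws. The baseline marker value is already needed for the planned repeated-measures ANOVA. The legend of Fig. 1 can be read as adding immunoblots only at the end, so confirm that a baseline blot is run.

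The limitation is that the adjusted model assumes data missing at random and cannot recover the missing day-28 outcomes. A mixed model should not be presented as restoring intention-to-treat.

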## Subjects and methods

### Study design and settings

This is a triple-blinded (investigators, statistical analysts, and participants), single-centered, randomized placebo-controlled, prospective intervention trial. This protocol is written following the Standard Protocol Items: Recommendations for Interventional Trials (SPIRIT) checklist [37]. The study is designed to investigate the molecular action mechanisms of ω3 as antiinflammatory and anti-ER stress through GPR120 receptor in peripheral blood mononuclear cells (PBMC) and leukocytes of overweight and obese subjects with visceral obesity and non-alcoholic fatty liver disease (NAFLD). The study protocol was approved by the Ethics Committee of the Federal University of Sergipe (#80476517.2.0000.5546) and registered at the Brazilian Registry of Clinical Trials (#RBR-7x8tbx), on May 10, 2018, retrospectively registered: https://ensaiosclinicos.gov.br/rg/RBR-7x8tbx. All outpatients will be informed by study design before signing the informed consent form.

In the first part of the intervention (acute measurement [3 h after the first capsule intake]), the surrogate outcomes will be [1] ω3 fatty acid concentration in bloodstream, [2] association between GPR120 and βarr2 proteins, and [3] ω3 fatty acid concentration into PBMCs. In the second part, after chronic treatment (28 days of supplementation), the primary outcome will be considered the reduction (upper to 10%) in the TNFα and IL6 protein contents in PBMCs. Both parts of the intervention will be carried out in PBMC and leukocytes. Outcomes such as body weight, waist circumference, and glycemia will not be considered due to short supplementation time and study aim.

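### The contrasts stated for the primary proteins do not settle on a between-arm test of the day-28 effect, and a literal reading of the ANOVA gives a diluted one

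*Protocol article*

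**What the plan says.** Under Study design and settings, after 28 days of supplementation, "the primary outcome will be considered the reduction (upper to 10%) in the TNFα and IL6 protein contents in PBMCs". The trial is randomized and placebo-controlled, so the efficacy question is whether these proteins fall more on ω3 than on placebo.

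Data treatment and statistical aspects gives the analysis in three steps:

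- An ANOVA: "First, a two-way analysis of variance will be performed to check intra- and intergroup differences". Its structure, in which the last group named enters as covariates, is: "Time will be added as a repeated factor, treatment as an independent factor, and the other variables (e.g., anthropometric data, food intake, blood analysis) as".
- Within-arm tests: the paired Student's t "test or Wilcoxon’s test will be used to compare the time effects".
- Between-arm tests: the Student's t "test and Mann-Whitney *U* test will be used to investigate group differences (placebo and treatment"). The text does not say whether these use day-28 values, change scores or something else.

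Every test is judged at P<0.05. The section does not mention the time × treatment interaction, a difference in change between arms, or a day-28 comparison adjusted for the pre-dose value. It does not say which test decides.

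Sample size calculation rests on a comparison of two groups with d = 1.15, "considering the variation of TNFα/βactin protein observed in the study by" a cited study, with power of 85% and 16 per group.

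**The concern.** In an ANOVA with time repeated and treatment between subjects, the term for a larger fall on ω3 than on placebo is the time × treatment interaction. The two purposes the plan gives for its ANOVA, differences within and between groups, correspond most directly to the two main effects. The follow-up tests repeat the same pair: time effects, then group differences.

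Neither main effect answers the trial's question.

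- **Treatment main effect.** It compares the arms on the average of the pre-dose and day-28 values. The pre-dose value cannot carry an ω3 effect, so the difference between arms is halved.
- **Time main effect, and the paired tests.** These ask whether values moved over 28 days. A shift common to both arms can make them significant when ω3 does nothing.

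An analyst who follows the wording literally could therefore miss an effect of the planned size, or report a within-arm fall as efficacy. With several tests at P<0.05 and none designated, two could disagree with no rule to settle it.

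**Working it through.** **Inputs from the protocol.** d = 1.15, α = 0.05, power 85%, 16 per group, 40% dropout and 22 per group selected (Sample size calculation).

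**Assumptions.** Two-sided testing; equal SD (set to 1) before and after; no true difference between arms before dosing; the whole effect present at day 28. The protocol gives no pre/post correlation r, so it is varied from 0 to 0.9.

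**Step 1: the plan's own figure.** For a two-sided two-sample comparison at d = 1.15 and 85% power, the normal formula gives 14 per group, the exact t calculation 15, and the Mann-Whitney version (relative efficiency 0.955) 16. The stated 16 is reproduced. At 16 per group the t test has noncentrality 1.15 × √(16/2) = 3.25 on 30 df, and power of 88%.

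**Step 2: standardised effect for each contrast.**

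- Day-28 t test: d
- Treatment main effect: (d/2) / √((1+r)/2)
- Time × treatment: d / √(2(1−r))
- ANCOVA on day 28, adjusted for pre-dose: d / √(1−r²)

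At r = 0.5:

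- Treatment main effect: 0.575 / √0.75 = 0.575 / 0.866 = 0.66
- Time × treatment: 1.15 / √1 = 1.15
- ANCOVA: 1.15 / 0.866 = 1.33

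**Step 3: power at 16 per arm (noncentral t).**

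| r | Treatment main effect | Time × treatment | Day-28 t test | ANCOVA |
|---|---|---|---|---|
| 0 | 60% | 60% | 88% | 88% |
| 0.3 | 50% | 76% | 88% | 91% |
| 0.5 | 44% | 88% | 88% | 95% |
| 0.7 | 40% | 98% | 88% | 99% |
| 0.9 | 37% | >99% | 88% | >99% |

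For the treatment main effect to reach 85%, 29 (r = 0) to 53 (r = 0.9) evaluable participants per arm would be needed. If 40% of 22 are lost (22 × 0.6 = 13.2, so 13 per arm), the day-28 t test has 80% and the treatment main effect 30% to 51%.

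**Step 4: the time effect when ω3 does nothing.** Let both arms shift by 0.5 SD, with r = 0.5. The change has SD √(2 × 0.5) = 1. With 32 participants the noncentrality is 0.5 × √32 = 2.83 on 30 df, and the time effect is significant about 78% of the time. A paired test within one arm of 16 (noncentrality 0.5 × √16 = 2 on 15 df) is significant about 46% of the time. In simulation of the same case the interaction and the day-28 t test rejected in about 5% of runs.

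**Step 5: sensitivity to d.** The same section reports: "the control group showed 0.45±0.04 (average of arbitrary units ± standard deviation) for TNFα while the telmisartan treated group showed 0.36±0.04". Those figures give (0.45 − 0.36)/0.04 = 2.25. At that d the treatment main effect keeps 88% to 99% power with 16 per arm. The loss in Step 3 therefore belongs to the planned d = 1.15. A 10% fall from 0.45 with SD 0.04 is 0.045/0.04 = 1.125, close to the planned value.

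**The case against.** The strongest reply is that the text lists purposes, not F-tests. A time-by-treatment ANOVA ordinarily yields the interaction, and nothing excludes it. The next sentences also plan a between-arm t or Mann-Whitney test which, on day-28 values, has 88% power and matches the two-group basis of the sample size. A journal article may leave the exact model term to a fuller document.

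Much of this stands. Three stronger readings are tempting and not supported:

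- *That the plan reads only the two main effects, so its power collapses.* This is an inference from the wording. That the ANOVA is run first gives an order, not precedence over the later t test.
- *That the time effect is evaluated at covariate = 0 and so has almost no power.* The section names the software ("The software Statistical Package for Social Sciences (SPSS), v. 22.0, will be used for data entry and analysis") but says nothing about centring. With one uncentred BMI-like covariate (assumed mean 30, SD 4), simulated power for the time effect is 6–8%. That rests on an assumed covariate and way of entering it, and it concerns a term that is not a between-arm contrast even when centred. The interaction is almost unaffected.
- *That the p-values are wrong.* With no ω3 effect the treatment main effect rejects at about 5%. It is valid, only weaker at the planned effect size.

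What the reply does not remove is that the article goes beyond silence. It states the model, the purposes and the follow-up tests, and none of the stated contrasts is the between-arm difference in change or an adjusted day-28 difference. The t test that could serve has no time point and no designated role.

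**Conclusion.** The point holds in limited form. The stated contrasts do not settle on the one that answers the primary question, and taken literally they lead to a weaker test or a non-comparative one.

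The loss under the literal reading is from 88% to about 44% at d = 1.15, 16 per arm and an assumed r of 0.5. Across r from 0 to 0.9 the treatment main effect has 60% down to 37%, so no value in that range restores the stated 85%. The size depends on d = 1.15, on the assumed r, and on reading the between-group purpose as the main effect. If the analyst uses a day-28 t test, the planned power is kept. The interaction also keeps it when r is about 0.5 or more.

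This should be corrected before analysis. It does not show that the plan as a whole is underpowered.

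**What to change.** In Data treatment and statistical aspects, replace the stated purpose of the ANOVA with wording such as: for each primary protein, the treatment effect is tested by one between-arm contrast, the day-28 value compared between arms with adjustment for the pre-dose value (ANCOVA), and reported as a difference with its 95% confidence interval. The time × treatment interaction is an acceptable alternative. ANCOVA is preferable because at 16 per arm its power is at least that of the day-28 t test for every r shown, whereas the interaction falls to 76% at r = 0.3 and 60% at r = 0.

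Add that the treatment and time main effects and the within-arm paired tests are descriptive and are not used to conclude on efficacy. If the between-arm t or Mann-Whitney test is kept, give its time point and call it supportive.

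Centring continuous covariates is a minor extra step, relevant only if the time effect is reported.

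The cost is a few sentences of analysis text. The pre-dose and day-28 values are already planned, so no further participants, samples or procedures are needed.
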